#### **6.17 Columbia Suicide Severity Rating Scale**

Consistent with regulatory guidance, the potential occurrence of suicide-related ideation and behaviors will be assessed in this Phase 1/2 study using the C-SSRS during Screening (C-SSRS baseline) and at the time points specified after Screening (C-SSRS since last visit).

The C-SSRS ([Posner et al 2010](#)) is a measure of the spectrum of suicidal ideation and behavior and was developed in the National Institute of Mental Health Treatment of Adolescent Suicide Attempters Study to assess severity and track suicidal events through any treatment. The C-SSRS consists of a clinical interview that can be administered during any evaluation or risk assessment to identify the occurrence and intensity of suicidal thoughts and suicidal behaviors. It can also be used during treatment to monitor for clinical worsening. If a suicide-related thought or behavior is identified at any time during the study, a thorough evaluation will be performed by a study physician and appropriate medical care will be provided ([DHSS, 2012](#)); the event will be reported as an AE or SAE.

Data from the C-SSRS will be included as part of the ongoing monitoring by the iDMC.

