reactions in spite of prophylactic corticosteroid treatment, a consultation with clinical immunologist should be considered. Immune response to the transgene protein (PGRN) is not expected in heterozygous haploinsufficient patients, as they naturally express PGRN at approximately 50% of normal levels.

Patients will receive a prophylactic steroid-sparing immunosuppressive regimen consisting of corticosteroids and sirolimus, intended to alleviate AAV9-related T-cell driven immune responses. Similar steroid-sparing approaches have demonstrated safety benefit and have been implemented in other gene therapy programs (e.g., [Bharucha-Goebel et al 2020](#); [Nevoret et al 2020](#)). Moreover, sirolimus has been shown to suppress AAV-related immune responses and increase transgene protein expression in NHPs ([Mingozzi et al 2007](#); [Ramsingh et al 2018](#)), is reported to be beneficial in animal models of FTD ([Wang et al 2012](#)), and has a manageable safety profile allowing the reduction or elimination of steroid usage ([Pidala et al 2020](#)).

Despite the beneficial effects of corticosteroids and sirolimus in the prevention and management of potential capsid and transgene immune reactions, both immunosuppressive agents are associated with a variety of adverse events (AEs). Systemic steroids at high doses can produce a variety of AEs ranging from mild irritability to life-threatening or even fatal biochemical effects including hyperglycemia, hypertension, and psychiatric disorders. A number of precautions should be considered with sirolimus usage, such as but not limited to increased risk of infections, malignancies/ lymphomas, angioedema, impaired wound healing, interstitial lung disease, hyperlipidemia, decline in renal function, proteinuria, embryo-fetal toxicity and male infertility. The use of live vaccines should be avoided during treatment with sirolimus. Sirolimus should not be used with strong CYP 3A4/P-gp inducers or inhibitors and requires monitoring of trough levels in the blood. If steroid or sirolimus side effects emerge, these drugs will be stopped or tapered as medically indicated.

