## **5.5 Investigational Product Administration**

### **5.5.1 Immunosuppressant Administration**

#### **5.5.1.1 Corticosteroid Administration**

Subjects will receive a loading dose of methylprednisolone 1 g IV pulse on Day 0. Prednisone at a dose of 30 mg/day will be given orally as concomitant medication from Day 1 for 14 days, which will be then tapered over the ensuing 7 days. At the Investigator's discretion, higher doses or a longer taper of corticosteroids may be used.

Mitigation of risks associated with use of corticosteroids, including monitoring for AEs that may be related to corticosteroid use are described in [Section 6.2.2.2](#).

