### **6.2.1.3 Eliciting and Documenting Adverse Events**

Adverse events will be assessed from the time the patient signs the ICF until exit from the study. Only AEs and SAEs determined to be related to a protocol-mandated intervention will be reported from the time the patient signs the ICF until ICM administration of investigational product. After ICM administration of investigational product, all AEs and SAEs will be reported.

At every study visit, patients will be asked a standard nonleading question to elicit any medically related changes in their well being. They will also be asked if they have been

hospitalized, had any accidents, used any new medications, or changed concomitant medication regimens (prescription and over-the-counter medications).

In addition to patients' observations, AEs identified from any study data (e.g., laboratory values, physical and neurological examination findings, ECG and MRI changes) or identified from review of other documents (e.g., patient diaries) that are relevant to patient safety will be documented on the AE page in the eCRF.

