#### **6.2.2.2 Risks Associated with the Use of Immunosuppressants**

One loading dose of 6 mg oral sirolimus will be administered at Day -1, as well as a single dose of 1 g IV methylprednisone at Day 0. A concomitant maintenance dose of 2 mg/day sirolimus will be administered orally for 90 days starting at Day 0 which will then be tapered over the ensuing 15 to 30 days. The maintenance dose is administered to achieve trough sirolimus concentration of 4 ng/mL (range 2 to 8 ng/mL). One day after treatment with PR006A, patients will start prednisone 30 mg orally for 14 days, followed by a 7-day taper. At the Investigator's discretion, adjustments of dose and duration are permitted.

Corticosteroids are administered for prophylactic suppression of inflammatory responses and to improve viral transduction. Despite the beneficial effects of prednisone and sirolimus in the prevention and management of potential liver enzyme abnormalities, systemic immunosuppressants in this dose range can produce a variety of AEs ranging from mild irritability to life-threatening or even fatal biochemical effects including but not limited to impaired wound healing, interstitial lung disease, hyperglycemia, hypertension, lymphomas/malignancies, hyperlipidemia, decline in renal function, proteinuria, embryo-fetal toxicity, and male fertility. While patients will be excluded if they are at increased risk of AEs, if corticosteroid side effects emerge, corticosteroids will be stopped or tapered as medically indicated. Glucose level checks, HbA1c, fructosamine, blood pressure, body weight, cholesterol, urine protein, lipids, red blood cell counts, neutrophil counts, protein glucose, CSF cell counts, CSF protein levels, CSF glucose levels, sirolimus trough concentrations, BMI, waist circumference, and psychosis incidence/aggravation will be monitored at study visits occurring during corticosteroid usage and after prednisone

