### **7.1 Primary Endpoints**

#### **7.1.1 Primary Safety Endpoints**

The following primary safety endpoints are measured up to 5 years:

- Incidence and severity of TEAEs and SAEs, including clinically significant changes in vital signs, clinical laboratory assessments, C-SSRS, and TNAS; treatment-emergent transaminitis; treatment-emergent diabetes and prediabetes; treatment-emergent peptic ulcer disease and/or erosive gastritis; treatment-emergent osteoporosis; treatment-emergent increase in body weight  $\geq 5\%$  from baseline, treatment-emergent BMI  $>25$  or  $>30$ , and treatment-emergent increase in waist circumference  $\geq 15\%$  from baseline; incidence of Grade  $\geq 3$  infections; incidence/aggravation of psychosis; treatment-emergent hypercholesterolemia or hyperlipidemia; treatment-emergent interstitial lung disease; treatment-emergent opportunistic infections (including progressive multifocal leukoencephalopathy (PML) and BK virus-associated nephropathy); sirolimus trough levels; 12-lead ECGs; brain MRIs; physical examinations; and neurological examinations
- Sum of ARs and suspected ARs
- Sum of serious ARs and serious suspected ARs
- Incidence of procedure or treatment-emergent safety findings as per brain MRI.
- Change from baseline in immunogenicity of AAV9 and PGRN in blood at Day 14 and Months 1, 2, 3, 6, 9, and 12 and in CSF at Months 2 and 12.

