| TMT-A, TMT-B                             | X                                 |                             |                |                |    |    |    |       |         |                 | X             |   | X                      | X             |
| Digit Span Test (forwards and backwards) | X                                 |                             |                |                |    |    |    |       |         |                 | X             |   | X                      | X             |
| C-SSRS (baseline)                        | X                                 |                             |                |                |    |    |    |       |         |                 |               |   |                        |               |
| C-SSRS (since last visit)                |                                   |                             |                |                |    |    |    | X     | X       | X               | X             | X | X                      | X             |
| TNAS                                     | X                                 |                             |                |                |    |    |    | X     | X       | X               | X             |   | X                      | X             |

| Visit Description                                                            | Screening/Baseline a,b |                             |                | Treatment      |    |    |    |    |         |                 |   |   |                        | Unscheduled |  |
|------------------------------------------------------------------------------|-----------------------------------|-----------------------------|----------------|----------------|----|----|----|----|---------|-----------------|---|---|------------------------|-------------|--|
|                                                                              | Day                               |                             |                |                |    |    |    |    | Month   |                 |   |   |                        |             |  |
|                                                                              | -35 to -2                         | Check-In
-1 c | 0 d | 1 e | 7  | 14 | 21 | 1  | 2       | 3               | 6 | 9 | 12/
ET f |             |  |

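### At nominal visit timing the default Day 0-21 steroid course has no scheduled C-SSRS; one mark at the existing Day 14 visit would close most of the gap

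*Protocol*

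**What the plan says.** Protocol Section 6.17 places a baseline C-SSRS at Screening and later ones "at the time points specified after Screening (C-SSRS since last visit"). It adds of the instrument: "It can also be used during treatment to monitor for clinical worsening". It requires a study physician to evaluate any suicidal thought or behavior that is identified, and it sends C-SSRS data to the iDMC.

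The row "C-SSRS (since last visit") in Table 13-1 is marked at Months 1, 2, 3, 6, 9 and 12/ET and in the Unscheduled column. Every earlier cell is blank.

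Section 5.5.1.1 gives the steroid course: a 1 g methylprednisolone pulse on Day 0, then prednisone 30 mg/day "given orally as concomitant medication from Day 1 for 14 days, which will be then tapered over the ensuing 7 days". Investigators may use higher doses or a longer taper. Table 13-1, footnote c, also lets sites give the pulse on Day -1.

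On risk, Section 1.3 says the effects of high-dose systemic steroids can extend to "fatal biochemical effects including hyperglycemia, hypertension, and psychiatric disorders". Section 6.2.2.2 states that "psychosis incidence/aggravation will be monitored at study visits occurring during corticosteroid usage and after prednisone" discontinuation. Section 7.1.1 defines the first primary safety endpoint as "including clinically significant changes in vital signs, clinical laboratory assessments, C-SSRS, and TNAS", among other items. Section 6.2.1.3 provides that at every visit "patients will be asked a standard nonleading question to elicit any medically related changes in their well being".

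**The concern.** The protocol recognises a psychiatric risk from high-dose steroids, schedules three visits within the default course, and has a suicidality instrument in its primary safety endpoint. It does not use that instrument at any of the three visits. Other steroid-related monitoring is placed there: fructosamine at Day 7, and blood chemistry and immunosuppressant compliance at Days 7, 14 and 21.

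What is at stake is the timing of detection. The physician evaluation in Section 6.17 starts only once a thought or behavior has been identified. During the course, identification depends on one of the following:

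- a report from the patient or the study partner;
- the general adverse event question or psychosis monitoring;
- an investigator's decision to do an unscheduled C-SSRS.

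If none of these brings ideation to light, it waits for the Month 1 interview. That interview then relies on recall by patients with dementia and on their study partners.

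**Working it through.** There is no figure in the plan to reproduce, so the check is a row count and calendar arithmetic.

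**Reading the table.** The main study schedule has 14 columns: Screening, Days -1, 0, 1, 7, 14 and 21, Months 1, 2, 3, 6, 9 and 12/ET, and Unscheduled. The vital signs row is marked in all 14, which confirms the alignment. The C-SSRS since-last-visit row has 7 blank cells (Screening to Day 21) followed by 7 marks. The baseline row is marked at Screening only.

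**Length of the course (Section 5.5.1.1).** Day 0 pulse (1) + Days 1-14 at 30 mg (14) + taper on Days 15-21 (7) = 22 days. The scheduled visits after discharge and within the course are Days 7, 14 and 21. With a C-SSRS: 0 of 3.

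**First scheduled post-dose C-SSRS.** The protocol gives no day number for Month 1. Assume Day 28 or Day 30, with the stated ±7-day window. Screening runs from Day -35 to Day -2 and can be extended with Sponsor approval.

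| Quantity | Month 1 = Day 28 | Month 1 = Day 30 |
|---|---|---|
| Visit window | Days 21-35 | Days 23-37 |
| Days after last 30 mg dose (Day 14) | 21-14 = 7 to 35-14 = 21 | 23-14 = 9 to 37-14 = 23 |
| Days after last taper day (Day 21), nominal | 28-21 = 7 | 30-21 = 9 |
| Days after last taper day, with window | 0 to 14 | 2 to 16 |
| Days back to the Screening C-SSRS | 21+2 = 23 to 35+35 = 70 | 23+2 = 25 to 37+35 = 72 |

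Only under the Day 28 assumption, at the extreme early end of the window, does Month 1 touch the course, and then only on the last taper day.

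**Effect of a Day 14 assessment (window ±2, Days 12-16).** Nominally it comes 28-14 = 14 or 30-14 = 16 days earlier than Month 1. With both windows the gain is 21-16 = 5 to 35-12 = 23 days, or 23-16 = 7 to 37-12 = 25 days.

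**Effect on dosing reviews.** The iDMC reviews come at least 8 weeks (56 days) after the second staggered patient is dosed. The latest Month 1 visit for that patient is Day 35 or Day 37, which is 56-35 = 21 or 56-37 = 19 days earlier. Month 1 C-SSRS data therefore precede those reviews.

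**The case against.** The strongest reply is that nothing is stated wrongly. Section 6.17 promises the C-SSRS only at the scheduled time points, and Table 13-1 supplies them. The sentence on monitoring for clinical worsening describes what the instrument can do and commits nobody to using it at these visits. A reader might infer that the protocol contradicts itself; it does not.

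The step from steroids to suicidality is also an inference. Section 1.3 names psychiatric disorders in general. The psychiatric event singled out under the immunosuppressant regimen in Section 6.2.2.2 is psychosis, and that is monitored during the course.

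The other safeguards are substantial:

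- exclusions 5i (psychiatric diagnoses that may interfere with study procedures and assessments) and 5j (recent ideation with intent, or suicidal behavior);
- 24-hour inpatient observation after dosing (Section 5.5.3);
- patient-initiated contact if symptoms develop (Section 6.2.1.1);
- study-partner input (inclusion criterion 10);
- stopping or tapering steroids if side effects emerge;
- an unscheduled C-SSRS whenever there is concern.

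The study manuals, which are not available here, may add more.

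All of this stands, and it reduces the consequence. It does not remove the gap, because none of these measures in the protocol is a scheduled, prompted question about suicidality during the course. The adverse event question is deliberately nonleading. An unscheduled C-SSRS needs prior suspicion. Exclusion 5j does not remove patients with ideation without intent, and psychiatric manifestations of FTD do not bar entry.

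Two further inferences go too far. One is that the primary safety endpoint loses these weeks. If the Month 1 form is read as covering the time since the previous C-SSRS, it includes them retrospectively; only a literal reading from the Day 21 visit would leave them out. The other is that the iDMC's dosing decisions are compromised, which the dates above do not support.

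**Conclusion.** The point holds as a cheap safety improvement. At nominal visit timing, no C-SSRS is scheduled between Screening and Month 1, so the 22-day default steroid course contains no scheduled, prompted suicidality assessment (0 of 3 visits). The likely consequence is limited to later or missed detection of ideation that nobody reports.

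The conclusion rests on the default regimen, since extended steroids could overlap Month 1, and on Month 1 falling at about Day 28 to Day 30. The day counts measure delay and are not an estimate of risk, for which the protocol gives no basis.

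**What to change.** In Table 13-1, mark C-SSRS (since last visit) at the existing Day 14 visit. Full-dose prednisone ends there and a physical examination is already scheduled. A further mark at Day 7 or Day 21 is optional. Unless the study manuals already do so, it would also help to state that each since-last-visit form covers the time since the previous C-SSRS.

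The cost is one short added interview per patient, so 15 in the planned sample, in people with dementia and at a visit they already attend. The change needs a routine protocol amendment with IRB/IEC approval (Section 11.2.1), but no new visit.

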### **6.18 Treatment-Induced Peripheral Neuropathy Assessment Scale**

The TNAS is a 9-item patient-reported outcome measure that rates symptom burden associated with treatment-induced peripheral neuropathy (TIPN). Patients are first asked to assess the severity of five common symptoms of TIPN as experienced in their extremities in the past 24 hours on an 11-point Likert scale ranging from “Not present” to “As bad as you can imagine”; symptoms assessed include numbness, tingling, pain, hot or burning sensations, and coldness. Patients are also asked to rate 4 items assessing the worst level of interference experienced in the last 24 hours caused by symptoms of TIPN: Difficulty using hands or fingers, trouble walking, trouble with balance or falling, and disturbed sleep; these 4 items are rated on an 11-point Likert scale ranging from “Have not interfered” to “Interfered completely.” ([Mendoza et al 2020](#)).

## **7 Statistical and Analytical Plan**

A statistical analysis plan (SAP) will be prepared to provide additional details on the approach to analyze and display the data. The SAP will be finalized before the database is locked and prior to the formal interim and final analysis.

### **7.1 Primary Endpoints**

#### **7.1.1 Primary Safety Endpoints**

The following primary safety endpoints are measured up to 5 years:

- Incidence and severity of TEAEs and SAEs, including clinically significant changes in vital signs, clinical laboratory assessments, C-SSRS, and TNAS; treatment-emergent transaminitis; treatment-emergent diabetes and prediabetes; treatment-emergent peptic ulcer disease and/or erosive gastritis; treatment-emergent osteoporosis; treatment-emergent increase in body weight  $\geq 5\%$  from baseline, treatment-emergent BMI  $>25$  or  $>30$ , and treatment-emergent increase in waist circumference  $\geq 15\%$  from baseline; incidence of Grade  $\geq 3$  infections; incidence/aggravation of psychosis; treatment-emergent hypercholesterolemia or hyperlipidemia; treatment-emergent interstitial lung disease; treatment-emergent opportunistic infections (including progressive multifocal leukoencephalopathy (PML) and BK virus-associated nephropathy); sirolimus trough levels; 12-lead ECGs; brain MRIs; physical examinations; and neurological examinations
- Sum of ARs and suspected ARs
- Sum of serious ARs and serious suspected ARs
- Incidence of procedure or treatment-emergent safety findings as per brain MRI.
- Change from baseline in immunogenicity of AAV9 and PGRN in blood at Day 14 and Months 1, 2, 3, 6, 9, and 12 and in CSF at Months 2 and 12.

## 7.1.2 Primary Efficacy Endpoints

The following are the primary efficacy endpoints:

- Change from baseline in PGRN levels in blood at Months 1, 2, 3, 6, 9, and 12
- Change from baseline in PGRN levels in CSF at Months 2 and 12.

## 7.2 Secondary Endpoints

The following secondary endpoints, consisting of efficacy and safety measures will be measured from baseline to Year 1 and will be summarized by assessment time.

Corresponding changes from baseline will also be summarized for these measures.

### 7.2.1 Secondary Efficacy Endpoints

- Change from baseline in CDR plus NACC FTLN at Months 6 and 12
- Change from baseline in NfL levels in blood at Months 2, 6, 9, and 12
- Change from baseline in NfL levels in CSF at Months 2 and 12

[REDACTED]

- [REDACTED]
- [REDACTED]
- [REDACTED]
- [REDACTED]
- [REDACTED]
- [REDACTED]
- [REDACTED]
- [REDACTED]

A horizontal bar chart titled 'U.S. should take action to address climate change' showing the percentage of respondents who believe the U.S. should take action to address climate change, broken down by age group. The x-axis represents the percentage from 0 to 100. The y-axis lists age groups. The bars are black. The data is as follows:

| Age Group | Percentage |
|-----------|------------|
| 18-29     | 92         |
| 30-49     | 88         |
| 50-69     | 82         |
| 70+       | 78         |
| 18-29     | 75         |
| 30-49     | 62         |
| 50-69     | 58         |
| 70+       | 52         |
| 18-29     | 48         |
| 30-49     | 42         |
| 50-69     | 38         |
| 70+       | 32         |
| 18-29     | 28         |
| 30-49     | 22         |
| 50-69     | 18         |
| 70+       | 12         |

## 7.4 Sample Size Calculations

Fifteen patients (3 cohorts of 5 patients each) will be administered a one-time dose of PR006A (low, mid, [REDACTED] dose). The sample size is based on enrollment feasibility and clinical objectives rather than statistical rationale. The sample size chosen of 5 patients for the low-, mid-, [REDACTED] dose cohorts is considered to be sufficient for evaluation of the safety, tolerability, and immunogenicity of PR006A in each cohort. The sample size is not based on statistical power considerations.

## 7.5 Analysis Sets

The following analysis sets will be used in the statistical analyses:

- Safety Analysis Set, which will include all enrolled patients who receive investigational product.
- Treatment Analysis Set, which will include all patients in the Safety Analysis Set and who have at least 1 efficacy evaluation following the Baseline visit.

Patient information, safety, efficacy, and biomarker results will be summarized descriptively. No inferential analysis will be performed.

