### **4.2.2 Handling of Withdrawals**

Patients are free to withdraw from the study at any time. Patient participation in the study may be stopped at any time at the discretion of the Investigator or at the request of the Sponsor.

Since this study includes the provision of gene therapy as a single administration, all patients who receive investigational product should be strongly encouraged to complete visits for a minimum of AEs assessments, even if these happen via phone visit.

If a patient who received investigational product withdraws prematurely from the study for any reason, study site personnel should make every effort to complete the full panel of assessments scheduled for the end of treatment visit. Patients who withdraw during the treatment period will complete the Month 12 (Year 1) assessments, while patients who withdraw during the follow-up period will complete the Month 60 assessments. If the termination visit is more than 3 months prior to the scheduled Month 12 assessment, or more than 6 months prior to the Month 60 assessment for subjects who discontinue participation after Month 12, in addition to performing termination visit assessments, the investigator and study site personnel should make every effort to complete the Month 12 or Month 60 assessments, respectively, at the originally scheduled time points. The reason for patient withdrawal must be documented in the eCRF.

If a patient undergoes the administration procedure but for whatever reason does not receive investigational product, the patient may be withdrawn from the study with safety follow-up for 30 days.

In the case of patients being lost to follow-up, at least 3 documented attempts to contact the patients must be made and documented in the patients' medical records.

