## **6.2 Safety Assessments**

### **6.2.1 Adverse Events**

#### **6.2.1.1 Definitions of Adverse Events**

An AE is defined as any unfavorable and unintended sign (e.g., an abnormal laboratory finding), symptom, or disease temporally associated with the use of a drug, without any judgment about causality or relationship to the drug. Patients will be instructed to contact the Investigator at any time after enrollment into the study (i.e., after signing the consent form) if any symptoms develop.

After signed written informed consent is provided but prior to ICM administration of investigational product, only AEs and SAEs related to a protocol-mandated intervention will be reported. All other AEs and SAEs during this time period will be recorded as medical history. After the ICM administration of investigational product, all AEs and SAEs will be reported.

A TEAE is defined as any event not present before exposure to investigational product or any event already present that worsens in either intensity or frequency after exposure to investigational product.

The Investigator is responsible for reporting all TEAEs (and predose AEs and SAEs related to a protocol-mandated intervention) that are observed or reported during the study, regardless of their relationship to investigational product or their clinical significance. Where known, a diagnosis should be recorded rather than individual signs, symptoms, or laboratory results.

Treatment-emergent AEs that may be associated with corticosteroid use should also be monitored ([Section 6.2.2.2](#)).

Adverse events may include:

- Any abnormal laboratory test results (hematology, blood chemistry, or urinalysis) or other safety assessments (e.g., ECG, radiological scans, vital sign measurements, C-SSRS), including those that are accompanied by clinical symptoms, considered clinically significant in the medical and scientific judgment of the Investigator (i.e., not related to progression of underlying disease), or require a medical intervention or change in concomitant medications.
- Exacerbation of a chronic or intermittent pre-existing condition including either an increase in frequency and/or intensity of the condition.
- New conditions detected or diagnosed after study intervention administration even though it may have been present before the start of the study.

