### **6.2.1.5 Suspected Adverse Reactions/Adverse Reactions**

The following AEs will be considered as ARs:

- All AEs occurring within 1-month post-PR006A administration procedure
- All AEs assessed as at least possibly related to the injection procedure or to investigational product treatment by the Investigator or Sponsor
- All AEs for which the Investigator's causality assessment is missing or indeterminate

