### **7.7.1 Analysis of Primary Endpoints**

The primary endpoints (presented in [Section 7.1](#)) will be summarized with descriptive statistics, at all time points where these variables are collected. No inferential statistical tests will be performed using safety data. The Safety Analysis Set will be used for analyses of the safety endpoints. The Treatment Analysis Set will be used for analyses of the primary efficacy endpoints.

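### The safety set admits only patients who receive product, so a cisternal procedure stopped by a complication is missing from the summarised procedure-safety rates

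*Protocol*

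**What the plan says.** Section 7.5 of the protocol, repeated in the synopsis, gives the "Safety Analysis Set, which will include all enrolled patients who receive investigational product". Section 7.7.1 adds: "The Safety Analysis Set will be used for analyses of the safety endpoints". The only other set in Section 7.5, the Treatment Analysis Set, is a subset of this one.

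Section 4.2.2 describes a patient whom neither set can hold: "If a patient undergoes the administration procedure but for whatever reason does not receive investigational product". For that case "the patient may be withdrawn from the study with safety follow-up for 30 days".

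The primary safety endpoints reach beyond the product. Section 7.1.1 lists "Incidence of procedure or treatment-emergent safety findings as per brain MRI", and also the sum of adverse reactions. Section 6.2.1.5 counts among adverse reactions "All AEs assessed as at least possibly related to the injection procedure or to investigational product treatment by the Investigator or Sponsor".

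Section 6.2.1.1 ties emergence to the product: "A TEAE is defined as any event not present before exposure to investigational product", or one already present that worsens afterwards. For the period between consent and dosing, the same section says that "only AEs and SAEs related to a protocol-mandated intervention will be reported".

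**The concern.** The primary objective is the safety of PR006A as given by suboccipital injection into the cisterna magna, so the procedure is part of what is being assessed. The procedure endpoints are framed around the procedure, but the set in which they are analysed is framed around receipt of product.

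Harm can come before product. Section 5.5.3 has cisternal fluid withdrawn before injection, under general anesthesia or deep sedation, and Section 6.2.2.3 names hematoma, meningitis and puncture of neuronal tissue among the risks. A complication at that stage may be the reason why product is not given. Membership of the safety set then depends on the outcome being measured. With five patients planned per cohort, one such patient decides whether the summarised procedure-complication rate is zero.

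**Working it through.** **Plan's own figure.** Section 7.4 gives 3 cohorts of 5 patients: 3 x 5 = 15. It reproduces. The size is not based on power, and all analyses are descriptive, so no power calculation applies.

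**Path of one patient through the text.** Suppose the cisternal procedure is started, a complication occurs, and no product is given.

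1. Is the event collected? Yes. Section 6.2.1.1 requires pre-dose events related to a protocol-mandated intervention to be reported, and Section 4.2.2 provides 30 days of safety follow-up.
2. Is it a procedure-related adverse reaction? Yes, if assessed as at least possibly related to the injection procedure. Section 6.2.1.5 sets no condition of product exposure for this.
3. Is it a TEAE? No, because Section 6.2.1.1 requires exposure to product. Section 7.1.1 also names SAEs, and these carry no exposure condition.
4. Is the patient in the set used for the summaries? No. Sections 7.5 and 7.7.1 require receipt of product.

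Step 4 therefore removes the event from the adverse-reaction and SAE summaries even though steps 1 and 2 would let it in.

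**Size.** Inputs: 15 procedures started, 5 per cohort (Section 7.4); no replacement of withdrawn patients (Section 4.2.3). Assumption, not from the documents: exactly one procedure is aborted by a complication, and no other patient has one. Exact (Clopper-Pearson) 95% limits:

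- for 0/n, the upper limit is 1 - 0.025^(1/n);
- for 1/n, the lower limit is 1 - 0.975^(1/n), and the upper limit is the 0.975 quantile of Beta(2, n - 1).

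| | Product received (as planned) | All started procedures |
|---|---|---|
| All cohorts | 0/14 = 0% (0-23.2%) | 1/15 = 6.7% (0.2-31.9%) |
| One cohort | 0/4 = 0% (0-60.2%) | 1/5 = 20.0% (0.5-71.6%) |

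**How often it could matter.** With p the assumed chance that a procedure is aborted by a complication, the chance of at least one such patient among 15 is 1 - (1 - p)^15:

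| p | At least one in 15 |
|---|---|
| 1% | 14.0% |
| 2% | 26.1% |
| 5% | 53.7% |
| 10% | 79.4% |

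The documents give no value for p; the range only shows how the answer depends on it.

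**The case against.** A product-received safety set is conventional, and for the effects of PR006A it is the right set. The event is not lost either: it is reported, followed for 30 days and open to listing under Section 7.7. In an open-label, descriptive trial of 15 patients, a serious aborted procedure would be plain to anyone reading the SAE reports. The analysis plan, not shown here, could also add a procedure summary. All of this limits the point to the summary tables. Within those tables it stands: a listing does not correct a rate shown as 0%, and an added summary would leave the definition in Sections 7.5 and 7.7.1 as it is.

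A reader might infer four stronger things that the protocol does not support.

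- *That the stopping rules are weakened.* Section 4.2.4 makes no use of the analysis set. Its two-event criterion covers SAEs as well as TEAEs and includes persistent neurological symptoms attributable to the administration procedure. Another criterion covers Grade 3 or higher SAEs whether or not related to PR006A, and after a pause the iDMC evaluates all available data.
- *That the rates are necessarily biased downward.* Section 4.2.2 allows any reason for not giving product. An abort for access or product-preparation reasons involves no selection on outcome. The bias arises only when a complication causes the abort.
- *That the aborted patient comes on top of 15 dosed patients.* Section 7.4 does speak of fifteen patients being dosed, but Section 4.2.2 lets this patient be withdrawn and Section 4.2.3 excludes replacement. The denominators above follow that rule.
- *That the set should begin at the first immunosuppressant dose.* This would bring in patients who never had a procedure and goes further than the defect.

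One practical limit also stands. Section 4.2.2 does not say that the Month 1 safety MRI is kept for a withdrawn patient, so the MRI endpoint may have no observation for that patient.

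**Conclusion.** The gap is real and narrow. The protocol foresees a patient who has the procedure without product and makes procedure safety part of its primary endpoints, but then analyses those endpoints only in patients who received product. If a complication is what stopped dosing, the summarised procedure-complication rate leaves out that event and that patient. For one such abort the difference is 0/14 against 1/15 overall and 0/4 against 1/5 in the cohort. The intervals are wide and overlap heavily; what changes is whether any event appears in the table.

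This rests on one assumed abort caused by a complication, no other complications and no replacement. The exclusion itself follows from the text. It should be corrected, but it does not put the trial's safety reporting or its stopping rules in doubt.

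**What to change.** Add to Section 7.5 a set of all enrolled patients in whom the administration procedure was started, shown by intended cohort. In Section 7.7.1, use it for procedure-related AEs and SAEs, adverse reactions, and procedure findings on brain MRI where an MRI was obtained. State that procedure-related events are counted from the start of the procedure; widening the set alone would not be enough where a table is limited to TEAEs. Keep the product-received set for PR006A-specific and long-term tables. Make the change before the first formal interim analysis, so that the denominator is not chosen after an aborted procedure is known.

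The cost is one added definition and the matching table specifications. The AE side needs no new collection, because intervention-related pre-dose events are already reported. There are two downsides. The rate looks slightly less favourable if a procedure is aborted. Undosed patients are also followed for less time (30 days, against up to 5 years), and their pre-dose events are recorded only if related to an intervention. The tables should carry a note on this difference.
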